#### Analysis of economic and quality-of-life data

An incremental cost-effectiveness analysis will be conducted to estimate the value for money afforded by the M4bH intervention with and without IAQ feedback over and above usual care.

##### Intervention costs

The costs of providing M4bH with and without IAQ feedback will be calculated. Costs will include the staff time required to deliver the M4bH intervention and the cost of materials used. Additional costs in the IAQ feedback arm include the costs of the Dylos DC1700 and the time taken to provide feedback to the household.

##### Training costs

The costs of training of individuals to deliver the intervention will be calculated. Training requires staff time of the trainer plus staff travel cost. Staff time is based on the salary of the trainer and allocated on a cost per minute basis plus costs of materials. Training costs are divided by the number of trained adults at each site. Training cost per adult benefits from economies of scale whereby cost per adult decreases as the number of adults trained increases at a site.

##### Health care utilisation

Health care resource use data for each participating member of the household will be collected in all three trial arms at baseline and 3, 6, and 12 months’ follow-up. This data will allow the calculation of cost profiles for each individual based on local unit costs of care which are multiplied by quantities of resources consumed to calculate a per individual cost.

##### Quality-adjusted life years

EQ-5D [33, 34] will be used for adults aged 18 years and over, EQ-5D-Y [35, 36] for adolescents (11–17 years) and PedsQoL (version 4) [37] for children aged younger than 11 years at baseline and 3, 6, and 12 months’ follow-up to calculate changes in Quality-adjusted Life Years (QALYs) for all household members using local social tariff scores to derive health utilities. QALYs will be calculated by using the area under the curve between baseline and follow-up assuming a linear change between recorded points [40].

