##### Participant (and household) baseline assessment

Baseline data will be collected from households, and all consenting participants in the household, once informed consent has been provided and before randomisation of their mosque, using questionnaires.

The following data will be collected about the household:Presence of outside space; number of bedrooms; number of residents (adults and children); number of resident smokers (adults and children)Self-reported smoking restrictions, or lack thereof, in the homeNumber of shops that sell tobacco products in neighbourhoodPresence of household amenities (e.g. electricity, flush toilet, etc.)Type of fuel used for cookingPresence of mould/moisture in homes and any damage causedPresence of cattle/pets/poultry in homeMosque attendance

IAQ of the household will also be measured at baseline as 24-h mean levels of PM_2.5_ concentration using the Dylos DC 1700 meter.

The following data will be collected about all consenting participants in the household:Socio-demographic variables (date of birth, gender, education)Self-reported smoking behaviour (≥ 11 years only)St George’s Respiratory Questionnaire (SGRQ) ≥ 11 years; frequency and severity of respiratory symptoms for under 11 year-oldsHealth service useHealth-related quality of life: (EQ-5D-5 L for 18 years and over, Proxy version of the EQ-5D-Y: 1 for 11–17 year olds, PedsQL version 4.0 for under 11 year-olds)Attitudes, social norms, intentions and action planning, self-efficacy, and coping planning with regards to smoking and SHS exposure (≥ 18 years only)

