#### Assessment of cost-effectiveness

##### Base case analysis

The outcome for the cost-effectiveness analysis will be QALYs at 12 months and the cost-effectiveness analysis will be performed at this time point. The costs will include intervention cost and the cost of health resources during the 12-month period post randomisation. QALYs will be calculated during the same time period. An incremental cost-effectiveness analysis will be performed to estimate the incremental cost-effectiveness ratios (ICERs). Both costs and QALYs will be combined to calculate the incremental cost per QALY. ICERs will be calculated for M4bH and IAQ feedback over and above usual care, M4bH intervention only over and above usual care, and M4bH plus IAQ compared to M4bH alone.

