##### Uncertainty assessment

Sensitivity analysis is conducted by varying the cost components of the intervention to estimate the robustness of the cost-effectiveness ratios. Uncertainty around the decision to adopt the intervention will be assessed through a non-parametric bootstrap re-sampling technique. Bootstrapping has been proposed as an efficient approach for calculating the confidence limits for the ICER as its validity does not require any specific assumptions with regard to the underlying distribution. A cost-effectiveness acceptability curve (CEAC) will be plotted based on the outcomes of the 5000 bootstrap replications [41].

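### The plan derives QALYs for under-11s from PedsQL through social tariff scores, but PedsQL has no tariff, so the stated route gives no valid utility for these children

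*Protocol article*

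**What the plan says.** The section on quality-adjusted life years in the protocol article assigns one instrument to each age band: EQ-5D from 18 years, EQ-5D-Y from 11 to 17 years, and "PedsQoL (version 4) [37] for children aged younger than 11 years at baseline and 3, 6, and 12 months’ follow-up". The same sentence says that these data will be used "to calculate changes in Quality-adjusted Life Years (QALYs) for all household members using local social tariff scores to derive health utilities". The next sentence gives the formula: "QALYs will be calculated by using the area under the curve between baseline and follow-up assuming a linear change between recorded points".

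The base case analysis section makes this quantity the economic endpoint: "The outcome for the cost-effectiveness analysis will be QALYs at 12 months". It continues: "Both costs and QALYs will be combined to calculate the incremental cost per QALY". ICERs are planned for all three pairwise comparisons of the arms.

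The baseline assessment section lists the same age bands, including "PedsQL version 4.0 for under 11 year-olds", and names no other quality-of-life instrument for that group. The secondary outcomes section presents PedsQL (there spelled PedsQoL) only as a measure of quality of life.

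On uncertainty, the article states: "Sensitivity analysis is conducted by varying the cost components of the intervention". It adds a non-parametric bootstrap and an acceptability curve.

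**The concern.** One rule, tariff scoring, is applied to three instruments, and one of them cannot be scored that way. A social tariff is a table of population values for the health states that a preference-based questionnaire defines, on a scale anchored at dead = 0 and full health = 1. EQ-5D and EQ-5D-Y define such states. PedsQL does not: its items are summed into a profile score with no states to value and no anchor at dead. This is general knowledge about the type of measure. The article neither states it nor says anything against it.

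What is at stake is the economic conclusion. Cost-effectiveness belongs to the primary objective, non-smoking residents of any age can make a household eligible, and the Background stresses harm to children. If the rule is left as written, whoever runs the analysis must improvise a conversion for under-11s. If that happens after the data have been seen, the ICER denominator would combine EQ-5D utilities with numbers of another kind, and the choice of conversion could move the result.

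**Working it through.** The article states no figure for this quantity, so there is nothing to reproduce. The check is whether the stated rule can be carried out in each age band.

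**Step 1: instrument against rule.**

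| Age band | Instrument | Stated route to utility | Does the route apply? |
|---|---|---|---|
| 18 and over | EQ-5D (5L at baseline) | Local tariff | Yes, if a local value set exists |
| 11–17 | EQ-5D-Y (proxy version at baseline) | Local tariff | Yes in principle; the article names no value set |
| Under 11 | PedsQL version 4 | Local tariff | No; there are no health states to value |

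**Step 2: look for a repair elsewhere in the article.** The baseline, secondary outcome, QALY, base case and uncertainty sections contain no mapping from PedsQL to utility. They name no second, preference-based child measure and do not limit QALYs to those aged 11 and over. The sensitivity analysis varies only cost components. The bootstrap resamples whatever values it is given, so it cannot reveal an invalid utility.

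**Step 3: write out the QALY formula.** Measurements are at 0, 3, 6 and 12 months, that is t = 0, 0.25, 0.5 and 1 year. With linear interpolation, QALY = Σ wᵢuᵢ, where:

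- baseline weight = 0.25/2 = 0.125
- 3-month weight = 0.25/2 + 0.25/2 = 0.25
- 6-month weight = 0.25/2 + 0.5/2 = 0.375
- 12-month weight = 0.5/2 = 0.25

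The weights sum to 1, and the three follow-up weights sum to 0.875. Each weight must multiply a utility uᵢ. For an under-11 the plan supplies a PedsQL score instead, so the sum is undefined until a conversion is specified.

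**Step 4: how much the missing conversion matters (assumed values, not from the article).** Take a between-arm difference of 5 PedsQL points at all three follow-ups and a constant conversion of c utility units per point. The QALY difference per child is 5 × c × 0.875:

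| c (assumed) | QALY difference |
|---|---|
| 0.002 | 0.009 |
| 0.005 | 0.022 |
| 0.01 | 0.044 |

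The same PedsQL data give a fivefold range in QALYs according to a conversion that the article does not state. The assumed values show only this dependence. They do not predict the trial's result.

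**The case against.** The best defence is that the sentence is compressed. On this reading the tariff wording was meant for the instruments that have tariffs, and the algorithm turning PedsQL into utilities is a matter for a health-economics analysis plan that is not shown. PedsQL is to be collected at each follow-up, so no data are lost and a mapping can still be named before analysis. The defence is right that the problem can be repaired without new data. It does not remove the point. Had the article said only that QALYs would be calculated, silence on a mapping would be acceptable. Instead it names PedsQL, names the tariff route and extends both to every household member, and that stated rule does not work for under-11s.

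Two stronger readings are tempting, and the documents do not support them.

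- A reader might infer that the instrument changes when a participant turns 11 or 18 during follow-up, so that one person's curve joins two scales. The article gives age bands and visit times but never says whether the band is set at baseline or updated at each visit. That is an unstated operational rule, not an error in the text.
- A reader might infer that the whole base-case QALY cannot be computed. The failure is confined to under-11s. This point does not touch the EQ-5D and EQ-5D-Y calculations, although the local value sets still have to be named.

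The article also does not propose rescaling PedsQL from 0–100 to 0–1 and does not describe how members' QALYs are pooled, so it should not be criticised for either.

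A final objection concerns the remedy. Simply dropping under-11s from the QALYs would set full costs against partial benefits, because health-care costs are calculated for each participating member and intervention costs are shared by the household or mosque. It would also set aside a group central to the trial's rationale. Both points stand, and the fix takes account of them.

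**Conclusion.** The point holds for children under 11. As written, the route from PedsQL to utility does not exist, and the base-case cost per QALY is not valid for these children. The conclusion rests on the article's own sentence and on one premise from general methods knowledge, that PedsQL is not preference-based and has no tariff.

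The problem affects every participating child under 11, in all three ICERs. The effect on the ICERs cannot be quantified, because the article gives neither the share of household members under 11 nor any conversion. The effectiveness analysis of PM2.5 is unaffected. The text should be corrected before the economic analysis; the trial design and the data collected do not need to change.

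**What to change.** Amend the sections on quality-adjusted life years and base case analysis as follows.

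1. Limit tariff-based QALYs to members whose instrument is preference-based and has a value set, and name that value set. This must be checked for EQ-5D-Y as well as EQ-5D.
2. Make the costs and QALYs in each ICER cover the same people. State how under-11s' health-care costs are handled, and how shared intervention costs are treated when some household members contribute no QALYs.
3. Report PedsQL for under-11s on its own scale, as a quality-of-life outcome.
4. Bring under-11s into the ICER only through a prespecified, named mapping to utilities, with the mapping's uncertainty carried into the bootstrap and the acceptability curve. Show results with and without under-11s.

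The cost is a few sentences of text and some extra analysis, with no new data collection. The downside is that the ICER without mapping omits any health benefit to under-11s, which is why both versions should be reported.

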#### Assessment of cost-effectiveness

##### Base case analysis

The outcome for the cost-effectiveness analysis will be QALYs at 12 months and the cost-effectiveness analysis will be performed at this time point. The costs will include intervention cost and the cost of health resources during the 12-month period post randomisation. QALYs will be calculated during the same time period. An incremental cost-effectiveness analysis will be performed to estimate the incremental cost-effectiveness ratios (ICERs). Both costs and QALYs will be combined to calculate the incremental cost per QALY. ICERs will be calculated for M4bH and IAQ feedback over and above usual care, M4bH intervention only over and above usual care, and M4bH plus IAQ compared to M4bH alone.

##### Uncertainty assessment

Sensitivity analysis is conducted by varying the cost components of the intervention to estimate the robustness of the cost-effectiveness ratios. Uncertainty around the decision to adopt the intervention will be assessed through a non-parametric bootstrap re-sampling technique. Bootstrapping has been proposed as an efficient approach for calculating the confidence limits for the ICER as its validity does not require any specific assumptions with regard to the underlying distribution. A cost-effectiveness acceptability curve (CEAC) will be plotted based on the outcomes of the 5000 bootstrap replications [41].

#### Interim analyses

No interim analyses will be conducted.

### Process evaluation

The process evaluation will be carried out concurrently with the effectiveness and economic evaluations. The three key functions of a process evaluation for an effectiveness trial, identified by the MRC guidance for process evaluation [42] – mechanisms of impact, context, and implementation (including intervention fidelity) will be explored as secondary outcomes.

#### Mechanisms of impact

To capture the views and experiences of participants, all household head/lead participants in both intervention arms whose homes have been included in the follow-up sample will complete a short questionnaire at the end of the intervention, as part of month-3 follow-up, exploring which components of the M4bH intervention and IAQ feedback they engaged with, the acceptability of each component and any perceived benefits/non-benefits to themselves and their families including those which were unanticipated. A purposive sample of 15–20 participants, a mix of men and women from households who have/have not achieved SFH (based on PM_2.5_ scores) will be interviewed to explore key issues that emerged in the questionnaire; for example, any messages worded within the mainstream Islamic discourse that were seen to be particularly influential or inappropriate. Based on the team’s previous experience, to avoid participant fatigue with data collection, these interviews will be administered a few days after the questionnaire.

#### Context and implementation

In six purposively selected mosques (a mix of those scoring high and low on fidelity) the imams and *khatibs* who delivered the intervention will be interviewed to explore how contextual factors, such as the mosque environment and other social, economic, cultural, environmental and political factors, have influenced the delivery and impact of the interventions. These in-depth interviews will also explore implementation issues including perceptions of the potential reach of M4bH, likely obstacles and potential opportunities for scale-up of M4bH.

#### Intervention fidelity assessment

A fidelity index, mapped onto the behaviour-change techniques [43] that underpin the M4bH intervention, will be used to assess adherence to delivering the intervention. Each mosque will deliver the intervention for a maximum of 12 weeks. It is expected that there will be at least 360 intervention sessions over this period (one session per week × 12 weeks per mosque × 30 mosques). The researcher(s) will perform the fidelity check on 10% of the sessions (approximately 36 observation sessions in total) by observing 50% of sessions in six randomly selected mosques in the intervention arms (three mosques per each intervention arm). The researcher(s) will code the behavioural change techniques applied during the sermon using a standardised coding fidelity index.

#### Process evaluation data analysis

##### Quantitative data analysis

The quantitative data from the short process evaluation questionnaires will be analysed using descriptive statistics.

##### Qualitative data analysis

The qualitative data from the short process evaluation questionnaires will be analysed using content analysis [44]. Interviews with imams and *khatibs* will be transcribed verbatim and translated into English and analysed using the Framework approach which is designed to address applied programme and policy-related questions [45]. NVivo 11 software will aid data handling. Integration of interview findings with respective short questionnaire data will be done using a ‘triangulation protocol’ [46].

##### Intervention fidelity data analyses

The intervention fidelity data will be analysed descriptively.

### Implementation and scale-up

Based on a recent review [47] of the success factors for scaling up public health interventions, the implementation and scale-up phase will involve three activities:

#### Budget impact analysis

A budget impact analysis will be conducted using secondary data to calculate the number of households who might benefit from the implementation of the M4bH intervention, both with and without feedback, and the associated cost of monitors. Based on estimates of the numbers of households, the budget impact of providing the M4bH intervention to all households who might benefit, both with and without a monitor, will be estimated. This component is important as it will demonstrate the potential cost which would be taken into account when assessing the affordability of intervention rollout.

#### Monitoring framework development

A simple monitoring framework which could be efficiently employed as the intervention gets disseminated widely will be developed. An expert panel will first examine the evaluative framework used in the effect and economic evaluation within MCLASS II and develop a consensus on a set of measure that could replace it during scale-up of M4bH.

#### ‘Way Forward’ workshop

The findings of the two activities above, as well as the imam and *khatib i*nterviews during process evaluation, will be presented to policy-makers, development partners, and respective faith-based and civil society organisations in a final ‘Way Forward’ workshop. The finalised intervention resources will also be presented. Participants will be facilitated to consider ways to overcome the identified blocks to implementation and to plan how to optimise opportunities for effective scale-up.

## Discussion

The MCLASS II study focusses on reducing SHS exposure in homes as a means of reducing the burden of lung diseases in LMICs. There is a need for measures to protect non-smokers, particularly women and children from SHS exposure within the home. This study addresses a major evidence gap in this area, which is partly responsible for no clear guidance on how to implement smoking restrictions and protect non-smokers from SHS exposure in homes.

The study evaluates an innovative intervention comprising messages to promote SFH embedded within the Islamic discourse and delivered by faith leaders – imams and *khatibs –*to their congregations, with or without IAQ feedback. If found to be effective in changing smoking behaviour in homes, such an approach could shift the existing smoking norms, i.e. reducing visibility of smoking in social spaces and de-normalising it for children who might otherwise take up smoking. Previous studies in South Asia (one in Pakistan and another in Bangladesh) showed promise in community-based approaches in reducing visibility of smoking in social spaces and promoting SFH [48, 49]. In addition, research findings from this study are likely to be generalisable, particularly to those communities that are facing high tobacco-related disease burden with similar smoking norms, and places a high value on faith-based settings and leaders in their public and private lives. The intervention also lends itself for adaptation and to be used in influencing other unhealthy behaviours through faith-based settings resulting in improving family health in ways that goes beyond to what is proposed here.

With IAQ measurements for 1800 households at baseline, the study will provide a large dataset on the magnitude of SHS exposure within the home, as well as any key issues around IAQ measurement, in Bangladesh. IAQ feedback has a potential to bring about change in smoking behaviour in or around the home for some individuals [50], thus can complement other community-based interventions such as M4bH.

The effectiveness-implementation hybrid design utilised in this study has a distinct advantage of allowing for the gathering of data on the delivery of an intervention during an effectiveness trial that inform its potential for implementation and scaling up in the ‘real world’. MCLASS II will be conducted with active engagement of policy-makers, a range of implementers and target communities. The intervention and its implementation will be tailored to the local context, which will be informed by qualitative research within target communities. A strong political will exists among policy-makers who are fully aware of the disease burden associated with SHS, the relevant gap in policy and its implementation, and the potential benefit of addressing SHS exposure in homes. Their engagement and interest in this and the other two MRC-funded studies on SFH in Bangladesh is evidence of the priority given to this area. Costs will be measured, economic modelling of scaling up SFH conducted, and an efficient monitoring framework developed. These are key success factors for implementation and scale-up [47]. Moreover, to enhance the impact of the research, a robust dissemination strategy will be offered consisting of (1) engagement with, and contributing to, policy groups through existing membership of policy advisory boards and working groups (WHO policy advisory groups, and The International Union against Lung Disease and Tuberculosis policy sub-groups); (2) working with the IF and the Ministry of Religious affairs to ensure incorporation of the M4bH training package within imams and *khatibs* training curricula; and (3) producing effective dissemination materials, i.e. policy briefs, publications in high-impact journals, presentations and seminars at conferences, press releases, media reports, web-publishing, and social media feeds. It is anticipated that the results of this study will be published in 2020.

All these elements of the study have the potential to influence policy and practice on tobacco control, particularly SHS exposure, in Bangladesh (Additional file 1).

